### Risk stratification: ESC guideline–based RISC score

Patients will be risk-stratified using the pre-defined ESC guideline–based RISC score (*Figure 2*). This score is calculated by assigning 1 point to every high-minor feature and 2 points to every high-major feature (*Table 1*). All patients will then be classified in three groups: low- (0 points), intermediate- (1 point), and high-risk (2 points) of serious cardiovascular events (*Figure 2*). Additionally, patients with a low calculated risk but with ≥1 high burden feature are deemed intermediate risk; these features include trauma without admission indication, high symptom burden, documented 1A/1B asystole during a reflex syncope, or a combination with functional transient loss of consciousness (psychogenic pseudosyncope) (see *Table 1*).

**Figure 2 oeag078-F2:**
[figure not shown]
ESC-guideline based RISC-score calculation.

### Informed consent and ethical approval

This trial adheres to the 2025 ICH-GCP guidelines.^15^ Patient information folders will be distributed to low- and intermediate-risk syncope patients identified on the (C)ED. Adamant time is provided to evaluate their participation in the trial before signing the informed consent form. This trial has been approved by the Medical Ethical Committee of the Amsterdam UMC (NL-009238) and is registered on clinicaltrials.gov (NCT06472375).

### Randomization

Upon inclusion, participants will be randomized to either the intervention arm (immediate discharge) or the comparator arm (24-h telemetry monitoring). Randomization is performed using a web-based weighted variable block design. Both study arms will receive 5-day ambulatory Holter monitoring upon randomization in order to record endpoints with the same modality. Physicians are advised to manage these patients as they would following the local protocols, with as the only confining factors being the minimal 24-h observation period and cardiac rhythm observation.

### Baseline characteristics

For comparison of the groups, baseline characteristics will be collected; these entail the following: age, height, weight, country of birth, number of TLOCs within the last year, smoking, alcohol use, drug use, medication use, frailty, comorbidities, most probable diagnosis, and low-risk, high-minor, and high-major criteria.^1^

### Questionnaires and telephone consults

Patients in both study arms were asked to complete questionnaires assessing syncope recurrence, quality of life (SF12, SDF, and EQ-5D-5L), and societal costs (iMCQ and iPCQ). Questionnaires were administered during the first week, at weeks 2, 3, and 4, and at 1 year (Appendix A). Participants are contacted by phone at day 1, day 7, 1 month, and 1 year after enrolment to verify the endpoints (Appendix A).

### Holter monitoring

Immediately after randomization, both treatment arms will receive 5-day ambulatory Holter monitoring using the Philips ePatch®.^16^ Patients are required to wear the Holter for a minimum of 24 h with sufficient signal. Holter patches are reapplied when they are not securely fixated during the first 24 h to ensure complete registration in the first 24 h for the primary endpoint analysis. After the initial 24-h period, Holter patches are not reapplied. All Holter recordings are analysed using the Cardiologs Holter analysis platform by an experienced clinician, a second expert will perform an independent quality control review.^17^ All pre-defined rhythm disturbances will be reported (Appendix C), even if they are not part of the endpoints. In the event of clinically relevant findings, treating physicians are notified immediately. The ambulatory Holters are not monitored in real time, as not to affect healthcare costs. Treating physicians will not have standard access to the full Holter report; the Holter data are available on request, allowing researchers to assess the potential diagnostic yield of the Holter monitoring.

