## Rationale

The current reason for the admission of syncope patients is two-fold. First, admission is considered safe because, in the case of rhythm disorders, immediate treatment can be started. Second, admission for monitoring may provide additional diagnostic value, given the chance of witnessing recurrence during the first hours after the syncopal event.^14^ Therefore, the question posed for intermediate-risk syncope patients is two-fold as well: is it safe to discharge these patients, and does admission provide a diagnostic benefit? If intermediate-risk patients can be safely discharged but might profit from rhythm observation, the solution of immediate discharge combined with immediate ambulant Holter monitoring could greatly reduce healthcare costs. Similarly, if there is no diagnostic yield, ambulant Holter monitoring could be omitted as well.

Therefore, we propose the RISC trial to investigate the safety of immediate discharge and the clinical benefit of ambulatory Holter monitoring in low- and intermediate-risk syncope patients. Furthermore, it evaluates the true healthcare cost benefit, the effect on the quality of life, the societal costs, and healthcare burden from a patient perspective. Additionally, we aim to investigate the diagnostic efficacy of immediate rhythm observation and, if apparent, the optimal duration of ambulatory Holter monitoring. The RISC trial, therefore, aims to determine whether immediate discharge with or without ambulatory Holter monitoring is safe and if it is a clinically and economically appropriate alternative to 24-h in hospital cardiac rhythm monitoring in pre-defined low- and intermediate-risk syncope patients.

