### Endpoints

The primary safety endpoint consists of the composite of arrhythmia disorders (supraventricular tachycardia, sinus pauses or bradycardia, and ventricular tachycardia), pre-defined conduction disorders (second- or third-degree AV block), syncope recurrence, unexplained falls with injury, all-cause death, and cardiovascular death (Appendix B) at 24 h after randomization. All primary endpoints will be evaluated at 24 h. Subgroup analysis will be performed on the low-risk and intermediate-risk–only cohorts.

Secondary endpoints include clinically relevant diagnostic yield of Holter monitoring, total admission costs, number of syncope-related tests and consultations after 1 month, duration of in-hospital stay after randomization for both treatment arms (superiority), and differences in proportion of correct diagnoses in both arms. In addition, quality of life and societal costs are assessed using telephone consults and standardized questionnaires of the SF12, SDF, EQ-5D-5L, and study-adapted iMCQ and iPCQ (Appendix A). Although quality of life (measured as QALYs) may not differ due to the risk of the population closely resembling a normal population, there might be a difference in perceived safety and understanding affecting the quality of life indirectly.

All primary endpoint definitions are described in Appendix B. A critical event committee centrally reviews all events that are potential endpoints.

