## Appendix B Study parameters / primary outcomes:

*Supraventricular tachycardia:*

- Any atrial tachycardia (sustained or non-sustained ≥ 3 consecutive complexes)
- Atrio-Ventricular Nodal Re-entry Tachycardia (AVNRT) or Atrioventricular Re-Entry Tachycardia (AVRT)
- Premature Atrial Complex (PAC): >2 doublets or >2 episodes of 3 s duration of bi- or trigemini and/or >5%
- Atrial Fibrillation *de novo*

*Ventricular tachycardia:*

- Any Ventricular Tachycardia (sustained/non sustained)
- Ventricular Fibrillation
- Premature Ventricular Complexes: >2 doublets or >2 episodes of 3 s duration of bi- or trigemini and/or >5%

*Conduction disorders:*

- Asystole >3sec (including conversion pauses)
- New first degree AV block with PQ > 300 msec
- Progression first degree AV block with 15%
- 2nd degree AV block Mobitz type I and II
- 3rd degree AV block
- Any SA block

*Other:*

- (near-)Syncope recurrence
- Unexplained fall with injury
- All cause death
- Cardiovascular death

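### The study Holter is fitted after the allocation is known, although the 24-h primary window opens at randomization; fitting it first closes a small ascertainment gap at almost no cost

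*Protocol article*

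**What the plan says.** The Endpoints section of the protocol article sets the primary composite "at 24 h after randomization", so the clock starts at randomization.

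Two sections place the recorder after that point. Holter monitoring: "Immediately after randomization, both treatment arms will receive 5-day ambulatory Holter monitoring". Randomization: "Both study arms will receive 5-day ambulatory Holter monitoring upon randomization in order to record endpoints with the same modality". The second also gives the purpose, which is one measuring instrument for both arms.

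The stated safeguard for the first day is that loose patches are put back on, "to ensure complete registration in the first 24 h for the primary endpoint analysis". No maximum fitting time is given, and nothing says that the patch is on before the allocation is disclosed.

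Care separates directly after allocation: "participants will be randomized to either the intervention arm (immediate discharge) or the comparator arm (24-h telemetry monitoring").

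**The concern.** The common Holter is the plan's main protection against finding more events in one arm simply because that arm is watched more closely. Most of the components in Appendix B are ECG findings, and many can be silent, for example "Any atrial tachycardia (sustained or non-sustained ≥ 3 consecutive complexes"). The day-1 telephone call cannot recover those. That the Holter will supply most of the events is an inference from this list; the article gives no breakdown.

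With the stated order, the instrument starts after the clock and after patient and staff know the arm. Reapplying a loose patch cannot cover time before the first fitting. One patient is about to go home and the other is about to be transferred, so the start of a good signal, and whether a patch goes on at all, can depend on the arm. Events missed in the discharge arm lower its observed rate and favour noninferiority. Events missed equally in both arms shrink a true difference. Events missed only in the admission arm cost power.

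**Working it through.** **Inputs from the article (Statistical considerations; Data analysis and bias).** Event rate 18% in both arms, margin 9 points, one-sided α 2.5%, 80% power, 10% loss, total 640, Farrington–Manning test on the rate difference.

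**The plan's own figure.** n per arm = (1.960 + 0.842)² × 2 × 0.18 × 0.82 / 0.09² = 286.05, so 287. Allowing for 10% loss: 287 / 0.9 = 318.9, so 319 per arm and 638 in total. The stated 640 is reproduced. It leaves 320 × 0.9 = 288 evaluable per arm, with power of about 80%.

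**Assumptions (not in the article).** Events fall uniformly over the 24 h, each can be seen only once, and the whole composite depends on the patch. A gap of g hours then hides a share f = g/24 of an arm's events, and the observed rate is p × (1 − f). This is an upper bound for a given gap under uniform timing.

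- 10 min: f = 0.167/24 = 0.69%, or 0.19 points of a 27% rate.
- 30 min: f = 0.5/24 = 2.08%, or 0.56 points of 27% and 0.38 points of 18%.

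**Type I error.** Put the truth at the margin, 27% against 18%, and ask how often noninferiority is declared. For a 30-min gap in the discharge arm only:

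- Observed discharge rate = 0.27 × (1 − 0.0208) = 0.2644, so the expected difference is 0.0844.
- Standard error at 288 per arm ≈ 0.0345.
- (0.09 − 0.0844) / 0.0345 − 1.960 ≈ −1.80, which gives a probability of about 3.6%.

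Exact enumeration of the Farrington–Manning test at 288 per arm gives:

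| Gap before adequate signal | Type I error at a true 9-point excess |
|---|---|
| none | 2.5% |
| 5 min, both arms | 2.6% |
| 10 min, both arms | 2.6% |
| 5 min, discharge arm only | 2.7% |
| 10 min, discharge arm only | 2.9% |
| 30 min, discharge arm only | 3.6% |
| 30 min, admission arm only | 1.9% |

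**Power.** With 18% in both arms and a 30-min gap in the admission arm only, the observed admission rate is 0.18 × (1 − 0.0208) = 17.6%. Power falls from 80% to 77%.

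With the patch recording before randomization, f = 0 in both arms and the planned 2.5% and 80% are kept. The sample size is unaffected.

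**The case against.** The strongest reply is that the article says the fitting is immediate. If sites keep to that, the gap is minutes and the error stays between 2.6% and 2.9%. This stands, and it is why the point is small. The wording sets no limit, however, and does not put fitting ahead of disclosure.

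The direction is also open. A patient going home has to be patched before leaving, while an admitted patient might be patched later on the ward. In that case the bias is conservative and the cost is power. This too is undocumented, and it stands.

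The calculation overstates the loss for a given gap. Several Appendix B criteria need repeated episodes or a burden above 5%, and these are rarely removed by losing a few minutes. Deaths, falls and syncope do not depend on the patch.

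Finally, a condensed article may leave fitting limits and site workflow to the full protocol. That is fair for the time limit, but the order of the steps is stated here, in two places.

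Four stronger readings are tempting and are not supported:

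- *Serious inflation of the false noninferiority rate.* Gaps of 1 or 2 h in the discharge arm alone would give 5.2% or 9.7% under the same model, but nothing in the article suggests such delays or that direction.
- *The first hours carry most of the yield, so early loss is worse than uniform.* The Rationale refers to "given the chance of witnessing recurrence during the first hours after the syncopal event". That clock starts at the syncope. Initial evaluation may take up to 4 h after arrival, and time for consent follows, so much of that period is over before randomization under either order.
- *The minimum 24 h of wear runs from fitting and so misses the primary window.* The Holter monitoring section does not say so; it ties the first 24 h to the primary analysis.
- *Unpatched patients are scored as event-free.* If 2% of the discharge arm alone were lost and counted this way, the error would be 3.6%; at 2% in both arms it would be 2.8%. The article states neither the loss nor the scoring, and the handling of missing recordings may be left to the analysis plan.

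**Conclusion.** The point holds as a small improvement in design. The primary window opens before the common recorder starts, and the start and uptake of recording are settled after an allocation that cannot be hidden. Recording can therefore be lost inside the window and can differ by arm.

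The documents establish neither the size nor the direction. On the assumed upper bound, plausible short gaps move the 2.5% error to between 2.6% and 2.9%. A 30-minute one-sided gap moves it to 3.6% or 1.9%, depending on the arm, with power of 77% in the latter case. The article does not support a claim that the noninferiority conclusion is compromised.

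**What to change.** In the Randomization and Holter monitoring sections, change the order of steps:

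1. After consent, fit the patch and confirm adequate signal.
2. Then randomize and disclose the allocation.
3. Mark the randomization time on the recording.
4. Read the primary Holter endpoints from randomization to 24 h, the same window as in the Endpoints section.

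The device and staff stay the same, and every randomized participant receives the patch in either arm anyway. The cost is a few patches used on patients who are never randomized, and a few minutes before allocation.

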### Endpoints

The primary safety endpoint consists of the composite of arrhythmia disorders (supraventricular tachycardia, sinus pauses or bradycardia, and ventricular tachycardia), pre-defined conduction disorders (second- or third-degree AV block), syncope recurrence, unexplained falls with injury, all-cause death, and cardiovascular death (Appendix B) at 24 h after randomization. All primary endpoints will be evaluated at 24 h. Subgroup analysis will be performed on the low-risk and intermediate-risk–only cohorts.

Secondary endpoints include clinically relevant diagnostic yield of Holter monitoring, total admission costs, number of syncope-related tests and consultations after 1 month, duration of in-hospital stay after randomization for both treatment arms (superiority), and differences in proportion of correct diagnoses in both arms. In addition, quality of life and societal costs are assessed using telephone consults and standardized questionnaires of the SF12, SDF, EQ-5D-5L, and study-adapted iMCQ and iPCQ (Appendix A). Although quality of life (measured as QALYs) may not differ due to the risk of the population closely resembling a normal population, there might be a difference in perceived safety and understanding affecting the quality of life indirectly.

All primary endpoint definitions are described in Appendix B. A critical event committee centrally reviews all events that are potential endpoints.

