### Statistical considerations

Immediate discharge (Intervention) is compared with discharge after 24-h in-hospital observation with rhythm monitoring (Comparator). We chose a prospective analysis due to the patient and physician bias, which would be inherent to a retrospective design. By application of 5-day ambulant Holter monitoring for all participants, we are able to compare all (non-)fatal events in both arms for which admission is strictly not mandatory (e.g. nonrhythm issues and/or later timing of nonfatal diagnoses). Based on studies on low- and intermediate-risk syncope patients in the setting of ED and in line with data from our own institute, we anticipate an event rate of 18% in both arms.^14,18–33^ By noninferiority, we aim to show that immediate discharge of these low-/intermediate-risk syncope patients is feasible and safe. With a noninferiority limit of 9% (for the difference in event rates, 50% of 18%), inclusion of a total of 640 patients with a one-sided type-1 error of 0025 provides the trial with 80% power (10% loss included). In the RISC trial, the noninferiority margin for the risk difference was set at 9% against an expected event rate of 18%, or half of the expected event rate. This margin is equivalent to a noninferiority margin of 1.50 for relative risk. The RISC trial’s noninferiority boundary is consistent with choices made for major landmark RCTs that influenced current guidelines (examples of RCTs are available upon request). In general, the choice of the noninferiority boundary has a major impact on the sample size needed for adequate power. A stricter noninferiority boundary would necessitate an impractically large sample size. For example, a noninferiority margin of 6% against an expected event rate of 18%, equivalent to a relative risk margin of 1.33, would more than double the sample size to 2 × 644. For the inclusion rate, based on the reference areas of the participating hospitals, the annual admissions of syncope on the emergency department, this will result in ≈ 50 eligible patients per year per centre.

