### Data analysis and bias

The main analysis is designed to evaluate whether immediate discharge (investigational treatment strategy) is noninferior to 24-h admission with continuous rhythm observation (reference treatment strategy) with respect to the primary composite endpoint of fatal and nonfatal events. The occurrence of the composite primary endpoint will be analysed in a statistical comparison of two proportions of (non-)fatal events. Rates of the primary endpoint are calculated as the proportion of patients in whom the primary endpoint has occurred. Rate differences are defined as the rate under the investigational treatment strategy minus that under the reference treatment strategy. The 95% confidence interval for the rate difference is calculated according to the Farrington–Manning method. Noninferiority of the investigational strategy of immediate discharge will be declared if the 95% confidence interval for the rate difference excludes 9%. Use of 95% confidence interval is equivalent to noninferiority testing with a one-sided type I error (α) of 2.5%. The one-sided *P* value for testing noninferiority with a margin of 9% is calculated according to Farrington–Manning method and must < 2.5% for rejection of the null-hypothesis of inferiority.

All of the analyses are carried out in the population of all randomized patients under application of the intention-to-treat principle, which implies that all primary endpoints are counted irrespective of the implementation of the randomized treatment assignment.

The follow-up period for each patient begins on the day of randomization and will be as long and continues for up to 12 months, with the aim of complete data collection. It is expected that the occurrence of the primary endpoint at 24 h will be known for all patients, except for those patients with early discontinuation of follow-up because of full withdrawal of informed consent.

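### A patient with a qualifying recorded arrhythmia is already a primary event, so syncope, injury or death in that patient within 24 h cannot move the noninferiority comparison

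*Protocol article*

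**What the plan says.** The Rationale section reports two reasons for admitting these patients. The safety reason is that "admission is considered safe because, in the case of rhythm disorders, immediate treatment can be started"; the other is diagnostic.

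The Endpoints section defines the primary outcome: "The primary safety endpoint consists of the composite of arrhythmia disorders (supraventricular tachycardia, sinus pauses or bradycardia, and ventricular tachycardia), pre-defined conduction disorders", plus syncope recurrence, unexplained falls with injury and death. On timing it says "All primary endpoints will be evaluated at 24 h". Appendix B sets the rhythm thresholds, some of them low, for example "Any atrial tachycardia (sustained or non-sustained ≥ 3 consecutive complexes".

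The Randomization section gives both arms the same recorder: "Both study arms will receive 5-day ambulatory Holter monitoring upon randomization in order to record endpoints with the same modality". The Holter monitoring section adds "The ambulatory Holters are not monitored in real time, as not to affect healthcare costs", and also says that treating physicians are told at once of clinically relevant findings.

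The Data analysis and bias section fixes the scoring: "Rates of the primary endpoint are calculated as the proportion of patients in whom the primary endpoint has occurred". Noninferiority is declared if the 95% confidence interval for the difference excludes 9 percentage points.

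The secondary endpoints listed are Holter yield, admission costs, tests and consultations, length of stay, correct diagnoses, quality of life and societal costs.

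**The concern.** Treatment prompted by a rhythm disorder can begin only after the disorder has occurred, and by then the patient is already a primary event. A ward patient who is treated at once without further trouble and a home patient with the same arrhythmia who later collapses, is injured or dies within 24 h both score one.

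The composite thus puts the trigger for treatment and the consequences that treatment might prevent into one yes/no variable, and the trigger is enough to settle its value. This does not depend on the minor ectopy in Appendix B. It would remain if only ventricular tachycardia, long pauses and high-grade block counted, although low thresholds enlarge the group in whom later events are absorbed.

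At stake is what a positive result can be said to show. The Statistical considerations section aims to show that immediate discharge is feasible and safe. For patients with a recorded arrhythmia, the test carries no information on clinical harm within 24 h, and none of the listed secondary endpoints supplies that comparison.

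**Working it through.** **Inputs from the documents.** Expected rate 18% in both arms (Statistical considerations: "we anticipate an event rate of 18% in both arms"); margin 9 points; one-sided type I error 2.5%; 80% power; total 640 including 10% loss; 1:1 allocation.

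**Reproducing the plan's figure.** Per arm, n = (1.960 + 0.842)² × 2 × 0.18 × 0.82 / 0.09² = 286.1, rounded up to 287. The total is 574, and 574 / 0.90 = 638, against 640 stated. The sample size reproduces and is not in dispute. Evaluable patients per arm: 640 × 0.90 / 2 = 288. Exact Farrington–Manning power at 18% v 18% with 288 per arm is 79.9%.

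**What the scoring rule can see.** Let A be a qualifying recorded arrhythmia within 24 h, and C be syncope recurrence, injurious unexplained fall or death within 24 h. The primary rate in each arm is

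P(A or C) = P(A) + P(C without A).

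The probability of C among patients with A does not appear. Any difference between arms in that quantity leaves the primary rates, and so the noninferiority decision, unchanged.

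**Numerical check (assumed rates).** Take P(A) = 15% and P(C without A) = 3% in both arms, and let half of the home patients with A go on to C, against none in hospital.

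- Primary: 15% + 3% = 18% in each arm; difference 0.
- Clinical events at home: 0.50 × 15% + 3% = 10.5%.
- Clinical events in hospital: 3.0%.
- Clinical difference: 7.5 points.

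Simulated trials (288 per arm, Farrington–Manning test, 4,000 trials per scenario) were run with P(A) of 12%, 15% or 17%, the total held at 18%, and the share of home arrhythmia patients with a consequence varied from 0% to 100%. Noninferiority was declared in about 79% to 81% of trials in every scenario, which is simulation noise of about 0.6 points around the planned power.

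**Plausible size of the hidden difference.** The documents give neither a rate of qualifying arrhythmia nor a rate of consequences, so both are assumed over a range. Hidden difference = (patients with A × share with a consequence at home) / 288, with none in hospital:

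| Patients with A, of 288 | 5% share | 50% share |
|---|---|---|
| 10 | 0.5/288 = 0.2 points | 5/288 = 1.7 points |
| 43 (15%) | 2.15/288 = 0.7 points | 21.5/288 = 7.5 points |

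**Precision of a separate comparison.** With 288 per arm and an assumed clinical event rate p in both arms, the approximate 95% half-width is 1.96 × √(2p(1−p)/288): 1.6 points at p = 1%, 2.8 points at 3%, 3.6 points at 5%.

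**The case against.** The strongest reply is that the composite already contains syncope, injurious falls and death. That is right as far as it goes. A reader might infer that the primary result is blind to all harm from not admitting, or that it measures arrhythmia occurrence only. The documents do not support either reading. Clinical events count in full in patients without a qualifying recorded arrhythmia, including events after a rhythm that does not qualify (such as known rather than new atrial fibrillation) or during a recording gap. A real difference in arrhythmia occurrence would also show. The blind spot is confined to patients who have both a qualifying arrhythmia and a clinical event within 24 h.

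A reader might also infer that the plan says discharge causes harm, or that arrhythmias at home go unanswered. The Rationale only reports why admission is considered safe; whether discharge is safe is the trial's question. Physicians are notified at once of clinically relevant Holter findings. Because the recording is not watched in real time, that notification follows a later reading, and it does not alter the scoring.

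The assumed consequence shares may be high for a population from which high-risk patients and likely cardiac diagnoses are excluded. This stands, and is why a range is given. Even its upper end lies below 9 points, so the illustration does not show a wrong verdict on the primary endpoint. That margin was, however, set as half of an 18% composite rate, not for syncope, injury and death alone.

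Finally, this is a condensed article, its secondary list is introduced as inclusive, and a tabulation by component may sit in an analysis plan not shown. That tempers the point but does not remove it. The decision rule is stated here and tied to a safety claim, and a tabulation of first events would lose the same later events.

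**Conclusion.** The point holds in this limited form. As written, the primary comparison cannot show whether immediate treatment of a rhythm disorder prevents syncope, injury or death within 24 h, because a patient with a qualifying recorded arrhythmia is counted regardless of what follows. That conclusion follows from the endpoint definition and the once-per-patient proportion, and needs no assumed rates.

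Its size cannot be derived from the documents. Under the assumed range (10 to 43 of 288 per arm with a qualifying arrhythmia, 5% to 50% of those at home with a consequence, none in hospital) the unseen difference is about 0.2 to 7.5 percentage points. The sample size, margin and test are unaffected. Nothing here shows that discharge is unsafe; it shows that noninferiority on this composite does not by itself settle safety for patients in whom an arrhythmia is recorded.

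**What to change.** Keep the primary endpoint, margin and sample size. Add to the Endpoints section one prespecified key secondary safety comparison: the proportion of patients in each arm with syncope recurrence, unexplained fall with injury or all-cause death within 24 h of randomization, counted whether or not an arrhythmia was recorded first, reported as a rate difference with a 95% confidence interval. State in the Data analysis and bias section that the safety conclusion is read from the primary result together with this comparison.

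The cost is wording in the protocol and analysis plan. The events are already to be verified by telephone on day 1 and reviewed centrally as potential endpoints, so no new data item is needed; the committee has only to adjudicate clinical events in patients who already have a qualifying arrhythmia as well. The downside is few events, wide intervals and a descriptive result. A powered test is out of reach: at an assumed 5% rate with a margin of half that rate, it would need about 2,654 patients in total including 10% loss, and more at lower rates.
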